**Fig. 1 Fig1:**
[figure not shown]
Flow chart of the study

**Table 2 Tab2:** Schedule of assessments concerning patients and caregivers in the intervention arm

PROMs			Standard time points									Variable time points
			B	3 m	6 m	9 m	12 m	15 m	18 m	21 m	24 m	
**ID**	**PROMs by MSmonitor Plus, for MS patients, with or without a caregiver/partner**											
1a 1b	Actionable SF-Qualiveen	Screening questionnaire for bladder disorders.	X	X	X	X	X	X	X	X	X	
		In order to assess health-related quality of life of patients with urinary disorders in neurologic conditions	X	X	X	X	X	X	X	X	X	
2	Checklist	For individual tension strength	X	X	X	X	X	X	X	X	X	
3	MSIP	Multiple sclerosis impact profile	X	X	X	X	X	X	X	X	X	
4	MSIS-29	Multiple sclerosis impact scale 29	X	X	X	X	X	X	X	X	X	
5	NBD	Neurogenic bowel dysfunction score	X	X	X	X	X	X	X	X	X	
6	Quick Scan	Five questions about the impact of fatigue on daily life, the Modified Fatigue Impact Scale-5 item Version (MFIS-5) and eight questions about health-related quality of life, the Leeds MS Quality of Life (LMSQol) and the registration of medication use	X	X	X	X	X	X	X	X	X	Every day if needed
7	HADS	Hospital anxiety and depression scale. Consists of a depression scale and anxiety scale, both are determined by means of seven questions	X		X		X		X		X	
8	MSISQ-15	Questionnaire on intimacy and sexuality in multiple sclerosis (MS) or spinal cord injury	X		X		X		X		X	
9	MSQOL-54	MS-specific quality of life	X		X		X		X		X	
10	Natalizumab checklist	16 questions every 28 days, submitted 2 days prior to the infusion of natalizumab	X									Every 28 days, if needed
11	Do I have a schub	Consists of 4 questions that the patient must answer. This shows whether he/she should contact the doctor to check if they have a schub	X									Daily available
12	Diary	The patient can keep track of activities and moments of rest in order to gain insight into fatigue	X									Daily available
ID	**PROMs by eCRF, for patients, with or without a caregiver/partner**											
13	iMCQ	iMTA Medical Consumption Questionnaire	X	X	X	X	X	X	X	X	X	
14	iPCQ	iMTA Productivity Cost Questionnaire	X	X	X	X	X	X	X	X	X	
15	CFQ	Cognitive failure questionnaire	X		X		X		X		X	
16	EQ-5D-5L	Health questionnaire (Dutch version)	X		X		X		X		X	
17	IPA	Impact on participation and autonomy	X		X		X		X		X	
18	MSSES	MS Self Efficacy Scale	X		X		X		X		X	
19	PIH	Partners in Heath Scale	X		X		X		X		X	

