#### Cost evaluation outcomes

Total costs over a 2-year period will be estimated using a bottom-up (or micro-costing) approach, where information on each element of service used is multiplied by an appropriate unit cost and summed to provide an overall total cost [50]. The time horizon will be the same as the follow-up period of the main study: from baseline and then every 3 months until a total period of 2 years.

We will assess intervention costs, healthcare costs, patient and family costs, and costs outside the health care sector. For this study, we will develop a cost questionnaire specially designed for this group, based on existing questionnaires [51] which will measure all relevant costs aspects.

To measure the actual use of resources, data will be obtained using combined sources (registrations by professionals and cost questionnaire). Resources used related to the interventions will be based on the registered time all professionals spent on the treatment. Intervention costs will include all the costs that will contribute to the development and administration of the MPVC and CAU, for example costs of training and travel expenses. All use of resources by the patient and their family in and outside the health care sector will be measured by means of a cost questionnaire (EQ-5D-5L), in which they continuously record volumes of resource utilization during the follow-up period.

Costs will be calculated by multiplying volumes (resource use) with unit costs. For units costs we will used the Dutch cost guidelines [6, 52, 53]. Productivity costs will be calculated by means of the friction cost method, based on a the mean added value of the Dutch working population. The friction costs method takes into account production losses confined to the period needed to replace a sick employee. In case of uncertainty, we will use a conservative estimation (i.e. the lowest cost price). Cost prices will be expressed in 2022 Euro. If necessary, existing cost prices will be updated to 2022 using the consumer price index. Resource use measurement (costs) will be measured continuously (for details see cost measurement), outcomes for the economic evaluation study will be measured at pre-test before randomization to the two study groups and every 3 months thereafter.

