### Cost effectiveness analyses

Economic evaluations compare additional costs and additional outcomes of CAU to MPVC. This economic evaluation will involve a combination of a cost-effectiveness analysis (CEA) and a cost-utility analysis (CUA). In a CEA effects are presented in clinical outcomes. The primary outcome measure for the cost-utility analysis will be QALYs, based on the Euroqol utility scores [55]. In the CUA, the Incremental cost-effectiveness ratio (ICER) will be expressed as the incremental costs per QALY. This economic evaluation will be performed from a societal perspective, which implies that all relevant costs and outcomes will be taken into account. The economic evaluation study will be performed in accordance with the Dutch Guidelines of the National Health Care Institute [56].

Following the Dutch guidelines, an annual discount rate of 1.5% will be applied to the effects, and future costs will be discounted to their present value by a rate of 4% [56]. Our primary (base-case analyses) will be performed in accordance with the intention-to-treat principle, including data from all participants regardless of whether they received the intervention or not.

A baseline analysis will be performed to examine the comparability of groups at baseline for both costs and outcomes. If necessary, methods will be applied to check for differences at baseline [57]. To investigate whether data are normally distributed, a Kolmogorov-Smirnov test will be performed. Despite the usual skewness in the distribution of costs, the arithmetic means will be generally considered the most appropriate measures to describe cost data [58, 59]. Therefore arithmetic means (and standard deviations) will be presented. In case of skewness of the cost data, non-parametric bootstrapping will be used to test for statistical differences in costs between the intervention and control group. Non-parametric bootstrapping is a method based on random sampling with replacement based on individual data of the participants. The bootstrap replications will be used to calculate 95% confidence intervals around the costs (95% CI), based on the 2.5th and 97.5th percentiles.

The incremental cost-effectiveness ratio (ICER) will be determined based on the incremental costs and effects of intervention and control groups. The cost-effectiveness ratio will be expressed in terms of cost per outcome gained, the cost-effectiveness ratio will focus on the net cost per QALY gained.

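### Economic evaluation: whether baseline differences are handled depends on an observed comparability check with no stated trigger, instead of planned adjustment for baseline utility

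*Protocol article*

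**What the plan says.** All but one of the relevant statements are in the protocol article under *Cost effectiveness analyses*.

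- The outcome: "The primary outcome measure for the cost-utility analysis will be QALYs, based on the Euroqol utility scores".
- The check: "A baseline analysis will be performed to examine the comparability of groups at baseline for both costs and outcomes".
- The rule that follows it: "If necessary, methods will be applied to check for differences at baseline". A reference is cited; no criterion, covariate or model is named.
- The ratio: "The incremental cost-effectiveness ratio (ICER) will be determined based on the incremental costs and effects of intervention and control groups". The formula given for it has no baseline term.

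Under *Cost evaluation outcomes* the article adds: "outcomes for the economic evaluation study will be measured at pre-test before randomization to the two study groups and every 3 months thereafter". Tables 2 and 3 schedule the EQ-5D-5L in both arms at baseline and at 6, 12, 18 and 24 months, and the iMCQ and iPCQ at baseline and every 3 months.

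No other section makes baseline adjustment of QALYs unconditional. *Missing data* covers missing values only. The sensitivity analysis of the ICER gives cost prices and volumes as its example. *Randomization* stratifies by sex and MS type, so baseline utility is not balanced by design.

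**The concern.** Baseline utility usually predicts later utility, and it also enters a QALY directly when the QALY is computed as an area under the curve. A chance difference between the arms at baseline therefore reappears, in part, as a difference in QALYs. Planned regression on baseline utility removes that component in every trial. A rule that first looks at the balance and then decides removes it only when the imbalance is judged large enough.

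Three things are at stake. First, in the trial as realised, the QALY difference may reflect where the arms started as well as what the intervention did. Second, the estimate is less precise than the collected data allow. Third, treatment assignment is open and the trigger is undefined, so the choice to adjust is made on the trial's own data, where different analysts could decide differently. The primary MSQOL-54 comparison is not affected.

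**Working it through.** The article gives no figure for utility variance or QALY precision, so there is no stated result to reproduce on this point. The only design figure used is the sample size. With margin 8, SD 17.5, one-sided alpha 0.0125 and 80% power, a noncentral-t calculation gives 93 per arm (power 80.4%). Then 93 / 0.9 = 103.3, which rounds up to the stated 104.

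**Inputs**
- From the article: 104 per arm; EQ-5D-5L at 0, 6, 12, 18 and 24 months; ceiling ratios of EUR 20,000, 50,000 and 80,000 per QALY.
- Assumed: utility SD 0.20 (range 0.15 to 0.25); slope of later on baseline utility 0.5 to 0.7; QALY as trapezoid area under the curve; no discounting.

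**Step 1: chance imbalance at baseline**

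SE = SD × √(2/104). At SD 0.20 this is 0.20 × 0.1387 = 0.0277. At SD 0.15 and 0.25 it is 0.0208 and 0.0347.

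**Step 2: carry-over into the 2-year QALY**

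The trapezoid weights in years are 0.25, 0.5, 0.5, 0.5 and 0.25. Baseline has weight 0.25 and the later visits together have 1.75.

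Shift per unit of imbalance = 0.25 + 1.75 × slope = 1.125 (slope 0.5) to 1.475 (slope 0.7). Full carry-over would be 2, so it is partial.

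**Step 3: size at SD 0.20**

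| Baseline imbalance | Shift in QALY difference | Value at EUR 50,000 per QALY |
|---|---|---|
| 1 SE = 0.028 | 0.031 to 0.041 | about EUR 1,560 to 2,050 |
| 1.96 SE = 0.054 | 0.061 to 0.080 | about EUR 3,060 to 4,010 |

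Over SD 0.15 to 0.25 the one-SE value runs from 0.0208 × 1.125 × 50,000 ≈ EUR 1,170 to 0.0347 × 1.475 × 50,000 ≈ EUR 2,560. The second row applies only if *necessary* were taken to mean p < 0.05, which the article does not say.

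**Step 4: dependence on the assumed schedule and QALY method**

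If utilities were measured every 3 months, as the text under *Cost evaluation outcomes* implies, the multiplier would be 0.125 + 1.875 × slope = 1.063 to 1.438, and the one-SE shift 0.029 to 0.040. If the effect were utility at the last visit only, the shift would be the slope times the imbalance: 0.5 to 0.7 × 0.0277 = 0.014 to 0.019 utility units.

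**Step 5: simulation with no treatment effect**

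10,000 trials per setting, SD 0.20, 104 per arm, no dropout, equal correlation between visits, and an assumed p < 0.05 trigger for the conditional rule.

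| | Slope 0.5 | Slope 0.7 |
|---|---|---|
| SD of QALY difference, unadjusted | 0.043 | 0.049 |
| SD, adjusted only if p < 0.05 | 0.040 | 0.043 |
| SD, always adjusted | 0.030 | 0.026 |
| Correlation with baseline imbalance, unadjusted | 0.72 | 0.85 |
| Correlation, adjusted only if p < 0.05 | 0.56 | 0.68 |
| Correlation, always adjusted | about 0 | about 0 |

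The mean estimate was zero to within 0.0005 under all three rules, so none is biased on average. Planned adjustment removed 51% and 72% of the variance; the conditional rule removed 14% and 21%. The pieces agree: √(0.0312² + 0.0301²) = 0.043 and √(0.0409² + 0.026²) = 0.048, which match the unadjusted SDs to within 0.001.

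**The case against.** Several stronger readings are tempting, and the article does not support them.

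- *Any imbalance goes straight into the ICER.* It does not: an imbalance judged relevant would be handled, and carry-over of the rest is partial.
- *The plan only checks and never adjusts.* The wording allows this, but the preceding sentence already does the checking. The natural reading is loose English for controlling for differences, possibly by the method in the cited reference. This is at most a wording query.
- *The QALY difference is biased.* Over repeated randomisations it is not. The one-SE shift (0.031 to 0.041) lies within the sampling SD of the unadjusted estimate (0.043 to 0.049), and the planned bootstrap already reflects that variation.
- *The true QALY difference is near zero, so the imbalance settles its sign.* The article does not say this. Non-inferiority is defined on the MSQOL-54, and the stated hypothesis is that quality of life improves.
- *Costs are affected to the same degree.* No size can be given, because the article does not say how well baseline cost predicts later cost.

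It can also be said that a condensed article leaves the trigger, covariates and model to the full protocol or analysis plan. That is fair for the details. It does not answer the point, because the conditional structure is itself stated, and filling in a trigger would still leave adjustment dependent on observed balance. The bootstrap shows the extra variance but does not remove it.

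**Conclusion.** The point holds in a limited form. The article fixes a conditional rule without a trigger where planned adjustment is better and costs almost nothing. The consequences are partial carry-over of unhandled chance imbalance into the realised QALY difference, lost precision and a data-dependent choice. Under the assumptions in the working, the one-SE effect is 0.031 to 0.041 QALY. The direction does not rest on those assumptions: it needs only that baseline utility predicts later utility. The size does rest on them, since the article states neither the utility SD, nor the slope, nor the QALY method. The case is made for QALYs; for costs it is a reasonable extension of unknown benefit. This improves one of the trial's three parts, the economic evaluation, and leaves the primary clinical conclusion untouched.

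**What to change.** Replace the conditional sentence with:

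> Incremental QALYs are estimated by regression on arm, baseline EQ-5D-5L utility and the stratification factors (sex, MS type), whatever the observed baseline balance, refitted within each bootstrap sample; the unadjusted result is a sensitivity analysis.

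Incremental costs can be adjusted in the same way for baseline costs from the iMCQ and iPCQ. The comparison of the arms at baseline can stay as description, without deciding the model.

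In the same edit, state how the QALY is computed, and reconcile the 3-monthly measurement described in the text with the 6-monthly EQ-5D-5L in Tables 2 and 3.

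The cost is wording and a few lines of code. Baseline EQ-5D-5L, iMCQ and iPCQ are already scheduled in both arms, so no new data or patients are needed.

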### Setting

The study will be conducted at the MS Expertise Center of Isala Diaconessenhuis, Meppel location, Netherlands.

Isala is the largest general top clinical teaching hospital in the Netherlands with 6000 employees and 1100 beds. Isala is divided into 5 locations: Zwolle, Meppel, Steenwijk, Kampen and Heerde.

The study started in April 2021, followed by 1 year of inclusion and 2 years of follow-up. The last patient’s final study visit will be in 2024. The results should be finally analyzed in January 2025.

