### Outcomes

#### Clinical effectiveness

##### Primary outcome

Multiple Sclerosis Quality of Life (MSQOL-54). MSQOL-54 is a multidimensional measure of health-related quality of life that combines both generic and MS-specific items in a single instrument [48, 49]. This 54-item instrument generates 12 subscales along with two summary scores, and two additional single-item measures. The subscales are: physical functioning, role limitations-physical, role limitations-emotional, pain, emotional well-being, energy, health perceptions, social functioning, cognitive functioning, health distress, overall quality of life, and sexual functioning. The summary scores are physical health summary and mental health summary. The single item measures are satisfaction with sexual function and change in health.

The primary time point at which the effectiveness of MPVC is determined is 2 years.

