The ICER is calculated as follows. ICER = (Ci - Cc) / (Ei - Ec), where Ci is the annual total cost of both study groups, Cc is the annual total cost of the control group (treatment by usual means), Ei is the effect at three-year follow-up for the intervention and control group, and Ec is the effect at the last follow-up for the control group (treatment by usual means).

The robustness of the ICER will be checked by non-parametric bootstrapping. Bootstrap simulations will also be conducted in order to quantify the uncertainty around the ICER, yielding information about the joint distribution of cost and effect differences. The bootstrapped cost-effectiveness ratios will be subsequently plotted in a cost-effectiveness plane, in which the vertical line reflects the difference in costs and the horizontal line reflects the difference in effectiveness. The choice of treatment depends on the maximum amount of money that society is prepared to pay for a gain in effectiveness, which is called the ceiling ratio. Therefore, the bootstrapped ICERs will also be depicted in a cost-effectiveness acceptability curve showing the probability that intervention and control groups are cost-effective using a range of ceiling ratios. In The Netherlands, a ceiling ratio between at € 20,000, € 50,000 and € 80,000 per QALY exists, depending on the burden of disease [60].

Additionally, to demonstrate the robustness of our base-case findings, a multi-way sensitivity analysis will be performed. In the sensitivity analysis uncertain factors of assumptions in the base case analysis will recalculated in order to assess whether the assumptions have influenced the incremental cost-effectiveness ratio (ICER), for example by varying cost-prices and volumes between minimum and maximum [61].

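### The ICER terms are defined on the wrong groups and on mismatched periods, so the formula cannot be computed as printed and an analyst must choose how to repair it

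*Protocol article*

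**What the plan says.** The section Cost effectiveness analyses gives the operative rule as ICER = (Ci - Cc)/(Ei - Ec). It explains the cost terms thus: "where Ci is the annual total cost of both study groups, Cc is the annual total cost of the control group". The first effect term is explained as follows: "Ei is the effect at three-year follow-up for the intervention and control group". The second effect term is tied to a different time point: "Ec is the effect at the last follow-up for the control group".

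Elsewhere the article describes a different quantity:

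- Earlier in the same section, the ratio "will be determined based on the incremental costs and effects of intervention and control groups", with cost per QALY gained as its focus.
- Cost evaluation outcomes: "Total costs over a 2-year period will be estimated using a bottom-up (or micro-costing) approach". On the period covered, the same section adds: "The time horizon will be the same as the follow-up period of the main study".
- Setting: the start in April 2021 is "followed by 1 year of inclusion and 2 years of follow-up".
- Primary outcome: "The primary time point at which the effectiveness of MPVC is determined is 2 years".
- Tables 2 and 3: the last scheduled assessment in either arm is at 24 months.

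The ratio is to be read against ceilings of EUR 20,000, 50,000 and 80,000 per QALY. Effects are discounted at 1.5% a year and costs at 4%.

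**The concern.** An incremental ratio needs the intervention arm in Ci and Ei, the control arm in Cc and Ec, and one common period for all four. The printed definitions fail on each count. Ci and Ei refer to both arms. Ei belongs to a time point that the trial does not have, while Ec belongs to one that it does. Costs are per year, although the stated total and horizon are 2 years.

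The economic evaluation is one of the trial's three parts. The bootstrap, the cost-effectiveness plane, the acceptability curve and the sensitivity analysis all rest on this ratio. If the definitions stay as they are, someone must choose a repair, possibly after seeing the data in an open-label trial, and different repairs can put the result on different sides of a ceiling.

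**Working it through.** **Step 1: each term against the rest of the article.**

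| Term | As defined | Conflict |
|---|---|---|
| Ci | annual cost, both arms | incremental intent stated earlier in the section; 2-year cost total |
| Cc | annual cost, control arm | 2-year cost total |
| Ei | effect at three years, both arms | incremental intent; follow-up and schedules end at 24 months |
| Ec | effect at last follow-up, control arm | right arm, but not the time point used for Ei |

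Ei cannot be observed, so the formula taken literally yields no number.

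**Step 2: what plausible repairs would give.** The article states no cost, QALY or ICER, so there is no figure to reproduce. All inputs here are assumptions: annual cost EUR 21,000 (MPVC) and 20,000 (CAU); annual QALYs 0.72 and 0.70. Over 2 years, undiscounted, that is EUR 42,000 and 40,000, and 1.44 and 1.40 QALYs.

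Reference: (42,000 - 40,000)/(1.44 - 1.40) = 2,000/0.04 = EUR 50,000 per QALY.

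| Repair | Calculation | Result (EUR) | Reference / result |
|---|---|---|---|
| Arms corrected, annual cost, annual QALYs | 1,000/0.02 | 50,000 | 1.0 |
| Pooled mean for Ci and Ei, 2 years throughout | (41,000 - 40,000)/(1.42 - 1.40) | 50,000 | 1.0 |
| Arms corrected, annual cost, 2-year QALYs | 1,000/0.04 | 25,000 | 2.0 |
| Pooled mean for Ci and Ei, annual cost, 2-year QALYs | (20,500 - 20,000)/(1.42 - 1.40) | 25,000 | 2.0 |
| Arms corrected, annual cost, 3-year QALYs in both arms | 1,000/0.06 | 16,667 | 3.0 |
| Sum of arms for Ci and Ei, annual cost, 2-year QALYs | (41,000 - 20,000)/(2.84 - 1.40) | 14,583 | 3.4 |
| Pooled mean for Ci only, annual cost, 2-year QALYs | 500/0.04 | 12,500 | 4.0 |
| Sum of arms for Ci only, annual cost, 2-year QALYs | 21,000/0.04 | 525,000 | 0.095 (10.5 times too high) |
| Arms corrected, annual cost, 3-year MPVC minus 2-year CAU QALYs | 1,000/(2.16 - 1.40) | 1,316 | 38 |

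If both arms are pooled as a mean in numerator and denominator, both differences halve and the group error cancels. Under the sum reading, the control terms drop out and the result is the MPVC arm's average cost per QALY, not an increment. That factor depends on the inputs. With annual costs of 20,400 and 20,000 the reference is 800/0.04 = 20,000 and the sum reading gives 20,400/1.44 = 14,167, a factor of 1.4. With 19,000 and 20,000 the reference is -2,000/0.04 = -50,000 and the sum reading gives 19,000/1.44 = +13,194, so the sign changes.

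**Step 3: discounting.** With the second year discounted, the 2-year multipliers are 1 + 1/1.04 = 1.962 for costs and 1 + 1/1.015 = 1.985 for effects. The reference becomes 50,000 x 1.962/1.985, about 49,400. Annual cost over discounted 2-year QALYs is 1,000/(0.02 x 1.985), about 25,200. The halving barely changes.

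**Step 4: the ceilings.** If the ratio is halved, any true value between a ceiling and twice that ceiling is reported below it: 20,000 to 40,000, 50,000 to 100,000, or 80,000 to 160,000. A true EUR 60,000, for instance, would be reported as EUR 30,000.

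**The case against.** The best defence is that this is a slip in one sentence. The same section states the incremental intent correctly, the cost-effectiveness plane plots differences in cost and effect, and the 2-year horizon is explicit elsewhere. An analyst who follows the surrounding text would compute the right ratio, and neither the primary outcome nor the sample size is touched. The three years may simply be the calendar length of the study, one year of inclusion plus two of follow-up. All of that is fair, and it makes the intent recoverable. It does not remove the contradiction, because the faulty sentence is the one that tells the analyst how to calculate. That the article condenses a fuller document does not help either: the definitions are printed here and printed wrongly, not left out.

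Three stronger readings are tempting, and the documents do not support them.

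- A reader might infer that the published cost per QALY will be wrong by a factor of at least 2. The formula gives no number as printed, and reasonable repairs range from no error to very large errors in either direction. A factor of 2 arises only from particular mixtures, chiefly annual costs over 2-year QALYs.
- A reader might infer that taking the effect at the last follow-up is itself a mistake. It does not define accumulated QALYs, but the article also plans a cost-effectiveness analysis on clinical outcomes, where a value at 24 months is legitimate.
- A reader might infer that the acceptability curve must be rebuilt on net monetary benefit. That is a preference of method. The article already plans the joint bootstrap distribution, the plane and the curve, and the error in the definitions does not depend on that choice.

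**Conclusion.** The point holds as an internal contradiction in a stated rule. Ci and Ei are defined on both arms instead of the MPVC arm, Ei refers to a follow-up that does not exist and does not match Ec, and annual costs contradict the 2-year total and horizon. This conclusion rests on the article's text alone and needs no assumption.

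The documents do not fix the numerical consequence. The halving from EUR 50,000 to EUR 25,000 assumes that the arms are corrected, or pooled on both sides, and that annual costs are set against QALYs accumulated over 2 years. The example also assumes equal costs and QALYs in each year, and it places the true ratio exactly on a ceiling. It shows that a plausible misreading could change the conclusion against a ceiling; it does not predict that this will happen.

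**What to change.** Replace the definitions under Cost effectiveness analyses, and carry the same wording into the economic analysis plan before analysis:

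- Ci and Cc: mean discounted total societal cost over 2 years in the MPVC arm and in the CAU arm.
- Ei and Ec: mean effect in the MPVC arm and in the CAU arm over the same 24-month horizon. For the cost-utility analysis this is discounted QALYs accumulated over 24 months; for the cost-effectiveness analysis it is the clinical outcome at 24 months.

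Delete *both study groups*, *annual*, *three-year* and *intervention and control group* from the definitions.

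The cost is a change of wording. No new data are needed: Tables 2 and 3 already schedule the EQ-5D-5L and MSQOL-54 every 6 months and the iMCQ and iPCQ every 3 months, in both arms, to 24 months.
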